### Treatment regimens

There is no interference with the ongoing medical treatment, clinical care or planned follow-up appointments of the participants in primary or secondary care.

#### Control group

Participants continue with their routine care management in line with their clinical care team’s current recommendations.

#### Intervention group

Those randomised to the intervention group are invited to attend the MAP programme. The programme comprises four facilitated group sessions delivered in local community settings. The sessions are run approximately 2 weeks apart and last about 1.5 h. The first session takes place within approximately 1 month of consent.

The MAP programme was developed using an iterative process, including a literature review to identify effective strategies within this population, and co-production with patient and public involvement (PPI) and other stakeholder groups (including clinicians and nurses who work in primary care). The literature review guided a content focus on the key generic challenges for this patient group: mastering emotions, managing treatments and communicating with a range of carers (family and health care professionals). The group discussions informed the content and format of the programme to include both a focus on increasing physical activity as well as the generic self-management challenges. The design of the programme was theoretically informed by social learning theory [35] and focussed carefully on the role of the facilitator to support participants to explore their own beliefs, understanding and concerns related to living with two or more long-term conditions. The design of the programme was underpinned by a fundamental belief that individuals know what is best for their health, yet may be more informed in their decision-making by taking part in an open and honest discussion that focusses on increased knowledge and insight through shared experiences [36].

A draft programme was tested with patient volunteers using an iterative process of testing, feedback and modification until the programme was completed and ready to be utilised in the RCT. Given the diverse patient group, the primary focus of the MAP programme is on factors related to development of health-related self-management behaviours, rather than being disease-specific. Each of the four sessions focusses discussion on moving more as well as on a session-specific topic related to the generic self-management challenges: mastering emotions, managing treatments and effective communication. Increasing physical activity is encouraged by using pedometers and exercise resistance bands, which are given to intervention participants. All sessions include a section on physical activity, with the later sessions focussing on reviewing goals and progress. The main format is group discussion, but the programme is person-centred, with self-monitoring and individual goal setting a key part. Additional file 2 summarises the structure and content of the four sessions.

The sessions are delivered by a ‘non-disease specific expert’ facilitator who has received training on the content and ‘person-centred’ delivery style of the programme [37]. Adopting a person-centred delivery style of the sessions focusses the need for facilitators to use behaviours that support participant engagement and reflection by all participants. Facilitators are provided with a specific training curriculum to support the delivery of education sessions. They are encouraged to use personal reflection and peer review to maintain the quality of the delivery and are supported with mentorship from trainers attached to the research team. Delivery of a number of sessions will be assessed by a trained observer in order to provide a measure of intervention fidelity. A structured observation tool will be used to assess facilitator delivery of prescribed behaviours and behaviour change techniques [38], and the tool includes an assessment of ‘talk-time’ as a measure of quality of delivery [39].

Follow-up support to motivate and promote positive health behaviour changes [40, 41] and improved medication adherence [42] have been shown to be effective when provided as text messaging. In order to support long-term behaviour change, regular reminder and motivational text messages are sent using an established independent provider. The commencement, frequency and duration of the messages are based on the design protocols developed for other self-management programmes [43–45] as well as consultation with stakeholders. Message delivery is automated and unidirectional and incurs no cost to participants. Participants who wish to stop receiving the messages can text ‘STOP’ in a response text. Additional file 3 summarises the frequency and content of the messages.

### Study management

Clinical visits are managed by trained research staff, predominantly research nurses and health care assistants from the University Hospitals of Leicester NHS Trust. All research staff have been trained in and follow standard operating procedures (SOPs) when collecting the data. Written informed consent is obtained by a trained research nurse before any trial activities take place. Data are collected at three time points: baseline, 6 months (postal) and 12 months (Fig. 1 and Table 2). In addition to the primary and secondary outcome data, demographic data and medical history data (details of relevant history of disease, medications, relevant surgical interventions) are recorded.

**Table 2 Tab2:** Summary of outcome assessment schedule

Outcome measures	Method	Baseline	6 months	12 months
Physical activity	Accelerometer worn for 8 continuous days and data downloaded	√	√	√
	Recent Physical Activity Questionnaire [49]	√	√	√
Self-efficacy	Chronic Disease Self-Efficacy Scale [56]	√	√	√
	Self-Efficacy for Exercise scale [57]	√	√	√
Quality of life	EuroQoL EQ-5D-5L scale. Health-Related Quality of Life Instrument [53]	√		√
	Hospital Anxiety and Depression Scale [54]	√		√
Medication adherence	Adherence Starts with Knowledge 12 questionnaire (ASK-12) [52]	√		√
Lifestyle	Diet, smoking status, sleeping behaviour questions	√		√
Demographic information	Ethnicity, work status, marital status questions	√		√ (except ethnicity)
Biochemical outcomes	Non-fasting blood sample to measure lipid profile, HbA1c, kidney function	√		√
Anthropometric measures	Height, weight, body mass index, waist and hip circumferences	√		√
Clinical measures	Blood pressure, pulse rate and grip strength	√		√
Medical history and medication	Self-reported	√		√
Use of health care services	Self-reported			√

### Primary outcome

The primary outcome measure is change in objectively measured physical activity from baseline to 12 months using the GENEActiv wrist-worn triaxial accelerometer (GENEActiv model 1.1, ActivInsights Ltd., Cambridgeshire, UK) with a dynamic range of +/− 8 *g*, where *g* is equal to the Earth’s gravitational pull. Participants are asked to wear the GENEActiv accelerometer on their non-dominant wrist for 8 consecutive days (24 h), wearing the monitor from the date of the assessment visit or from a specified date when sent in the 6 months postal follow-up. The accelerometer is initialised to collect data at 100 Hz. An appropriately trained individual instructs the participant on correct placement of the monitor. Participants are asked to complete a log whilst wearing the monitor to provide their waking hours and wear time information. Participants are given a stamped addressed envelope in which to return the monitor and log sheet once completed. Accelerometer data will be calibrated and analysed according to best practice procedures through the Lifestyle Theme of the National Institute for Health Research (NIHR) Leicester Biomedical Research Centre. In brief, data will be processed and calibrated using a bespoke open source package in R (GGIR, http://cran.r-project.org) [46, 47] according to criteria previously described [48]. Data will be included if participants have one or more valid days of data, with a valid day defined as at least 16 h of wear time. The primary outcome is defined a priori as average movement intensity as quantified by the Euclidean norm minus 1 *g* (ENMO) method. In addition, time asleep, sleep quality and time in sedentary behaviour; light-intensity physical activity; and moderate to vigorous physical activity will also be derived using validated algorithms and thresholds.

### Secondary outcomes

The following secondary outcomes are collected at baseline and at 12 months, and a number are also collected at 6 months by postal questionnaire (Table 2).

#### Clinical measures

Blood pressure and resting pulse rate are measured after the participant has been sitting for 5 min using the Omron HEM-907 Digital Upper Arm Cuff Blood Pressure Monitor (Omron Corporation, Kyoto, Japan). Three measurements are made, and the first measurement is excluded when calculating the mean. Grip strength is measured using a Baseline Hydraulic Hand Dynamometer (Fabrication Enterprises Inc., White Plains, NY, USA) according to the standardised procedure. Three measurements are made on both hands, and the highest value is used in the analysis.

#### Blood tests

Venous blood samples are taken and sent for analysis of full lipid profile, kidney function (sodium, potassium, urea, creatinine and estimated glomerular filtration rate (eGFR) and glycated haemoglobin (HbA1c) in accredited laboratories at University Hospitals of Leicester NHS Trust. The samples are analysed in accordance with the laboratory’s SOPs and destroyed after analysis. All results are reviewed by the study clinician. Where results are abnormal and clinically significant, historical results from the previous 6 months are reviewed. If there have been substantial changes in any of the levels, a letter is sent to the participant’s general practitioner.

#### Anthropometric measures

Body weight (in kilograms) is measured using the bioelectrical impedance Tanita Scales BC-418-MA (Tanita Corporation, Tokyo, Japan) and height (in metres) using a portable stadiometer (Holtain, Crymych,UK). Weight and height are used to calculate body mass index (weight in kilograms/height in metres squared). Waist circumference (centimetres) is measured at approximately 1 cm above the iliac crest and hip circumference at the widest area around the gluteus maximus.

#### Questionnaire measures

##### Recent Physical Activity Questionnaire (RPAQ)

The RPAQ is designed to explore day-to-day physical activity levels in the previous 4 weeks. The questionnaire is divided into three sections: (1) physical activity patterns in and around the house, (2) travel to work and work activities and (3) recreational activities. The RPAQ has reasonable validity for measuring total physical activity levels [49, 50].

##### Adherence Starts with Knowledge 12 (ASK-12) questionnaire

The ASK-12 questionnaire is used to assess medication adherence. It is a validated tool containing 12 questions and was adapted from the validated ASK-20 questionnaire [51, 52]. Twelve patient-specific barriers are scored from 1 to 5 using a Likert scale. Sub-scales providing measures of inconvenience/forgetfulness, treatment beliefs and behaviour can be calculated as well as a total score (ranging from 12 to 60).

##### EuroQoL five-dimensional, five-level version (EQ-5D-5L)

The EQ-5D assesses health-related quality of life and provides useful data for health economic analyses. The EQ-5D-5L is a validated measure of health status and has been validated specifically in chronic conditions, such as cardiovascular disease. The EQ-5D-5L has five quality of life dimensions (mobility, self-care, usual activities, pain/discomfort and anxiety/depression) which are all coded between 1 and 5 [53].

##### Hospital Anxiety and Depression Scale (HADS)

The HADS is a validated 14-item questionnaire measuring the severity of symptoms of anxiety and depression [54]. The anxiety and depression scores are each calculated from 7 questions which are scored from 0 to 3 on a Likert scale. Upon completion, selected scores are totalled and reported for anxiety and depression individually.

##### Chronic Disease Self-Efficacy Scale (CDSES)

The validated 33-item CDSES [55, 56] consists of three key concepts: self-efficacy to perform self-management behaviours, self-efficacy to manage disease in general and self-efficacy to achieve outcomes. In addition, the concepts are broken down into a number of sub-scales. All items are scored from 1 (not at all confident) to 10 (totally confident) using a Likert scale.

##### Self-Efficacy for Exercise (SEE) Scale

The SEE scale is a validated nine-item instrument that focusses on self-efficacy expectations related to the ability to continue exercising in the face of barriers to exercise [57]. The barriers are specifically related to weather, boredom, pain, exercising alone, lack of enjoyment, busyness, tiredness, stress and depression.

##### Lifestyle measures (diet, smoking status and alcohol consumption)

Dietary behaviour is captured using two short questionnaires based on dietary questionnaires developed for the European Prospective Investigation into Cancer and Nutrition (EPIC) study [58] and the international Nateglinide And Valsartan in Impaired Glucose Tolerance Outcomes Research (NAVIGATOR) study [59].

##### Use of health care services

These questions record the number of times in the past 12 months the participant has seen a general practitioner, practice nurse or other health care professional as well as details of prescribed and purchased medications and number of off-sick days.

### Economic evaluation

During the period of the trial the cost of running the MAP programme will be compiled from the unit costs mobilised in order to implement the service; this will include staff costs, room hire, costs of materials and resources utilised and participant travel costs. Data on health care utilisation will also be collected and will include both general practitioner and emergency department visits, hospitalisations and medication use. Research costs, such as those for clinic visits and blood tests, will be considered separately.

If the RCT finds no significant effect on clinical outcomes, a cost-consequence analysis will be undertaken. If a significant impact is found, cost-effectiveness analyses will be carried out for the outcomes that show a significant difference between the two trial arms. If the intervention shows a significant improvement in quality of life, then a cost-utility analysis will also be performed using preference-based health utility scores generated from the EQ-5D-5L questionnaire. Both a short-term cost-effectiveness analysis covering the period of the trial (12 months) and a Markov model using external data and projecting longer-term cost-effectiveness will be considered.

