## Methods/design

### Aims and objectives

The aims of this trial are to:Test the effectiveness of a structured self-management programme on increasing the levels of physical activity using accelerometry at 12 months in people with multimorbidityAssess the effectiveness of the programme on improving clinical measures including blood pressure, lipid profile, body weight and grip strengthAssess the effectiveness of the programme on improving self-management outcomes including medication adherence, lifestyle behaviours, clinical outcomes, quality of life and self-efficacyCarry out an economic evaluation of the intervention. This will assess implementation and running costs, as well as short-term and long-term cost-effectiveness

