### Sample size

The primary outcome is change from baseline to 12 months in average daily physical activity as quantified by ENMO and measured in milligravitional units (m*g*). In order to detect a minimum clinically significant difference of 2.1 m*g*, which is equivalent to an overall increase in physical activity volume of approximately 10 metabolic equivalent hours per week and is consistent with minimum recommendations for health, and assuming a standard deviation of 5.3 m*g* [60], a power of 80% and a significance level of 5%, the sample size requires 202 participants. To allow for 20% loss to follow-up and 20% non-compliance of accelerometer/intervention attendance, we will need to recruit 338 participants (169 in each arm).

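### The economic evaluation is gated on statistical significance, although the aim of assessing cost-effectiveness is unconditional and the trial is powered only for physical activity

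*Protocol article*

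**What the plan says.** The Economic evaluation section of the protocol article sets three conditional rules:

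- If nothing clinical is significant: "If the RCT finds no significant effect on clinical outcomes, a cost-consequence analysis will be undertaken".
- If something is significant: "cost-effectiveness analyses will be carried out for the outcomes that show a significant difference between the two trial arms".
- For cost per QALY, using utilities from the EQ-5D-5L: "If the intervention shows a significant improvement in quality of life, then a cost-utility analysis will also be performed".

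The section adds that a 12-month cost-effectiveness analysis is under consideration, and so is a longer-term model: "a Markov model using external data and projecting longer-term cost-effectiveness will be considered". Programme running costs and health care use are collected in every case.

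The last item under Aims and objectives describes the economic evaluation without any condition: "This will assess implementation and running costs, as well as short-term and long-term cost-effectiveness".

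The Sample size section powers the trial for one outcome only, the 12-month change in ENMO: "a power of 80% and a significance level of 5%, the sample size requires 202 participants". No power is given for EQ-5D-5L, QALYs or costs.

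**The concern.** Two things go wrong when the form of an economic evaluation hangs on p-values.

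First, the gate asks the wrong question. Whether a programme is worth its cost depends on the joint distribution of incremental cost and incremental effect. A non-significant difference in quality of life is not evidence of no difference, and a small uncertain gain with offsetting health care costs may still be worth funding. Equally, a significant effect does not show value for money. Under the stated rule the trial can end with no cost per QALY, and with no cost-effectiveness ratio at all, although assessing cost-effectiveness is one of its declared aims.

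Second, the gate selects. An outcome enters a ratio only if its estimate is large relative to its standard error. On average such estimates overstate the true effect, so a ratio computed from them flatters the programme. The overstatement grows as power falls, and power is unstated for every outcome except ENMO.

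**Working it through.** **1. The plan's own figure.** Inputs from Sample size: difference 2.1 mg, SD 5.3 mg, 80% power, 5% level (taken as two-sided), 1:1 allocation. The t-test calculation gives 100.96, so 101 per arm and 202 in total, as stated. Inflation: 202 / (1 − 0.40) = 336.7, so 337, or 338 to keep the arms equal. The sample size reproduces and is not in dispute. It gives two plausible numbers per arm for EQ-5D-5L: 101 (the evaluable number) and 338 × 0.80 / 2 = 135 (20% loss to follow-up only).

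**2. Bias from reporting only significant estimates.** Let δ be the true effect divided by its standard error. For an estimate that is significant in the programme's favour at two-sided 5%, the average estimate divided by the truth is

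1 + φ(1.96 − δ) / [δ × Φ(δ − 1.96)].

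| Power | δ | Calculation | Average overstatement |
|---|---|---|---|
| 80% | 2.80 | 1 + 0.280 / (2.80 × 0.80) | 1.12-fold |
| 50% | 1.96 | 1 + 0.399 / (1.96 × 0.50) | 1.41-fold |
| 20% | 1.115 | 1 + 0.279 / (1.115 × 0.199) | 2.26-fold |

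For ENMO at 101 per arm the standard error is 5.3 × √(2/101) = 0.746 mg. A true 2.1 mg passes the gate 80% of the time and is then overstated 1.12-fold. A true 1.05 mg passes 29% of the time and is overstated 1.84-fold.

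**3. Chance that the cost-utility analysis is triggered (illustration).** The article gives no SD or expected difference for EQ-5D utility, so these are assumptions. It also does not state the level that defines a significant result in the Economic evaluation section; 5% is carried over from Sample size. The standard error is SD × √(2/n), and the chance of passing is about Φ(difference / SE − 1.96).

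*Unadjusted, difference 0.03:*

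- SD 0.25, 101 per arm: SE 0.0352, ratio 0.85, chance 14% (t-test 13.6%).
- SD 0.20, 135 per arm: SE 0.0243, ratio 1.23, chance 23% (t-test 23.3%).

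*With baseline adjustment.* The Statistical analysis section says secondary outcomes will be analysed by methods similar to the main model, which adjusts for baseline, and Table 2 shows EQ-5D-5L at baseline and 12 months. The standard error is then multiplied by √(1 − ρ²), where ρ is the baseline to follow-up correlation (assumed 0.5 to 0.8).

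- SD 0.25, 101 per arm, ρ = 0.5: SE 0.0352 × 0.866 = 0.0305, ratio 0.98, chance about 17%.
- SD 0.20, 135 per arm, ρ = 0.8: SE 0.0243 × 0.60 = 0.0146, ratio 2.05, chance about 54%.

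*Wider unadjusted range.* For differences of 0.02 to 0.05 and SD 0.15 to 0.25, the t-test chance runs from about 9% (0.02, SD 0.25, 101 per arm) to 78% (0.05, SD 0.15, 135 per arm). Adding ρ = 0.8 to that most favourable corner gives SE 0.15 × √(2/135) × 0.60 = 0.0110, ratio 4.56 and a chance above 99%.

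**4. The sections side by side.** The aim covers costs, short-term cost-effectiveness and long-term cost-effectiveness, with no condition. The methods deliver costs in every case. They deliver cost-effectiveness ratios only after a significant result, cost per QALY only after a significant quality-of-life result, and treat both the 12-month analysis and the longer-term model as things to consider. The two sections do not agree on what is promised.

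**The case against.** The case against has several good parts.

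- **The triggering probability is soft.** It rests on assumed EQ-5D values, and an unadjusted test is not what the protocol implies. A reader might infer from the unadjusted figures that cost-utility would be skipped about four times in five. The documents do not support that: it is the pessimistic end. With baseline adjustment and the same difference and SDs the skip rate is about 46 to 83%, and under favourable assumptions the gate would nearly always be passed.
- **The aim is not wholly at risk.** Programme costs are compiled regardless, and a cost-consequence analysis is a recognised form of economic evaluation. What can be lost is the ratio, in particular cost per QALY.
- **Inflation is small where power is good.** For an outcome whose true effect equals the design value it is about 1.12-fold.
- **The Markov model.** A reader might infer that inflated effects are carried into the long-term projection. The article says only that such a model will be considered, using external data, and does not state which trial estimates would feed it.
- **False positives.** With 10 independent outcomes, all truly null, the chance of at least one significant result is 1 − 0.95^10 = 40%; with 20 it is 64%. Several of the listed outcomes are clearly correlated (weight, body mass index, waist, hip), so these figures show only the direction of the problem.
- **Method detail.** Bootstrapping and acceptability curves may properly be left to a health economics plan, and their absence from an article is no fault.

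All of this limits the size of the point. None of it removes the gate, which is a stated rule and not an omission, and nothing else in the article lifts it.

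**Conclusion.** The point stands in a limited form. The Economic evaluation section fixes a rule under which the type of analysis, and the outcomes that enter it, depend on significance. That rule does not match the unconditional aim, and it is a poor basis for judging value for money.

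The structural part needs no assumed EQ-5D values: any effect admitted only on significance is biased away from zero, by about 1.1-fold at 80% power, 1.4-fold at 50% and 2.3-fold at 20% (normal theory, two-sided 5%). The chance that cost-utility is triggered is illustrative: 14 to 23% unadjusted and about 17 to 54% adjusted for a difference of 0.03 and SD 0.20 to 0.25, and about 9 to 78% unadjusted over the wider range. The width of that range shows that whether a cost per QALY will be produced cannot be told from the plan.

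The randomised clinical comparison, the primary analysis and the sample size are unaffected. The point merits a change but does not threaten the trial's main conclusion.

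**What to change.** State in the Economic evaluation section, or in the analysis plan still to be approved before database lock, that two analyses will be done whatever the p-values:

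- a within-trial cost-utility analysis, with cost per QALY from EQ-5D-5L;
- a within-trial cost-effectiveness analysis on the primary outcome.

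Report the joint uncertainty in cost and effect for both, and keep the cost-consequence table in every case. If the Markov model is run, say that its trial inputs are the estimated effects with their uncertainty and are not limited to significant ones. Bring the Aims and objectives and Economic evaluation sections into line on what is committed and what is only under consideration.

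The cost is wording and modest extra analysis. EQ-5D-5L is already collected at baseline and 12 months and health care use at 12 months, so no new data and no change in sample size are needed. The downside is that the intervals may be wide, but they would show honestly what the trial can say about value for money.
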